##### Blood pressure outcomes

Office mean, systolic, and diastolic blood pressure assessments will be obtained using a calibrated and automated oscillometric device (HEM-7156t, OMRON, China). Participants will be kept in a calm environment for 5 min, after which measurements will be taken in both arms of the participant. Three measurements, with an interval of 1 to 2 min, will be taken in the arm with the highest initial value. The average of the three measurements is considered the subject’s office blood pressure.

##### Blood pressure and heart rate reactivity

Blood pressure and heart rate reactivity will be measured as the difference between values recorded during a mental stressor and those obtained at rest. The Stroop Test [50] will be used to induce mental stress, presented via a video on a screen in front of the participant for 3 min. Every 2 s, a visual stimulus consisting of a word written in a specific color will appear, with the color of the word and its meaning being incongruent (for example, the word "blue" written in red). The participant must respond verbally and as quickly as possible to the color of the letters, ignoring the meaning of the word.

Throughout the test, systolic and diastolic blood pressure will be assessed by the auscultatory method, using a stethoscope and a calibrated aneroid sphygmomanometer (Littmann Classic III, United States), with one reading every minute, for a total of three readings. The reference arm is the same one used for resting BP assessment. Heart rate will be measured at the same time points using a heart rate monitor (H10, Polar, Kempele, Finland). After completing the test, participants will be asked to rate their perceived stress level using a subjective stress scale proposed by Callister et al. [51], with the following ratings: 0 = not at all stressful; 1 = slightly stressful; 3 = very stressful; or 4 = extremely stressful. Additionally, the number of errors made during the test is recorded as an indicator of cognitive performance.

##### Heart rate variability

Heart rate variability (HRV) will be measured with participants seated at rest for 10 min, during which time their heart rate will be continuously recorded using a heart rate monitor (H10, Polar, Kempele, Finland), a validated and widely used device for HRV analysis. Data collection will take place in a quiet environment with a controlled temperature between 24 and 26 °C. Data will be collected via Bluetooth and stored in the Polar Flow app, later exported in a compatible format (.txt or.csv). The final 5 min of the resting period will be considered for analysis, as they offer greater physiological stability.

Data will be processed in Kubios HRV software, utilizing an automatic artifact correction feature with a low threshold filter. HRV analysis will follow the recommendations of the Task Force of the European Society of Cardiology and the North American Society of Pacing and Electrophysiology [52]. Considering the time domain, the parameters Standard Deviation of NN Intervals (SDNN), which reflects the global variability of autonomic activity, and Root Mean Square of Successive Differences (RMSSD), which is an index sensitive to parasympathetic activity and representative of short-term variations in RR intervals, will be determined. In the frequency domain, the Low Frequency (LF, 0.04–0.15 Hz), related to sympathetic-parasympathetic modulation, the High Frequency (HF, 0.15–0.40 Hz), linked to vagal (parasympathetic) modulation, and the LF/HF ratio, an estimate of the autonomic balance between the sympathetic and parasympathetic systems, will be determined. This set of parameters will allow the assessment of cardiac autonomic modulation and potential adaptations induced by the intervention.

##### Depressive and anxiety symptoms

The Brazilian Portuguese adaptation of HADS will be used to assess depressive and anxious symptoms [53]. It is an instrument composed of 14 items, with seven items forming the anxiety subscale and the other seven forming the depression subscale, allowing for the assessment of symptoms from the previous week. Each HADS item has four response options ranging from 0 to 3, and reaches a maximum of 21 points in each subscale. Participants will be instructed to answer the questions based on the last 7 days. Higher scores indicate more severe symptoms and a worse perceived emotional state.

##### Sleep quality

The validated Brazilian Portuguese version of the PSQI will be used to assess subjective sleep quality and related disorders [54]. The questionnaire consists of 19 items, grouped into seven components: subjective sleep quality, sleep latency, sleep duration, habitual sleep efficiency, sleep disorders, use of sleeping medications, and daytime dysfunction. Each component is scored from 0 (no difficulty) to 3 (severe difficulty), and the sum of the scores results in an overall score ranging from 0 to 21; scores greater than 5 indicate poor sleep quality.

##### Quality of life

Quality of life will be assessed using the WHOQOL-BREF questionnaire, developed by the World Health Organization and previously validated in the Brazilian population [55]. The WHOQOL-BREF comprises 26 items divided into four domains: physical, psychological, social relationships, and environment. This instrument is self-administered, utilizing a 5-point Likert scale, and yields standardized scores ranging from 0 to 100, with higher values indicating a better perceived quality of life.

#### Other outcomes

##### Cognitive status

The Brazilian Portuguese version of the MMSE, standardized by Brucki et al. [56], will be used to screen for cognitive decline. In the present study, it will be used to stratify randomization. The questionnaire is divided into two sections: the first, with a maximum score of 21, requires vocal responses regarding temporal and spatial orientation, memory, and attention; the second, with a maximum score of 9, assesses the ability to name, follow commands, write, and copy a polygon. The maximum total score is 30 points, and the test is not timed. Participants’ cognitive function is classified based on cutoff points adjusted for education, as proposed by Brucki et al. [56]. The score is formed by the sum of the items answered correctly; the higher the score, the better the cognitive function.

##### Sociodemographic and clinical characteristics

Sociodemographic data, health history, medical conditions, and medication use will be collected using a standardized questionnaire before the intervention.

##### Anthropometric assessment

Anthropometric outcomes will be measured at baseline and at the post-intervention period. Body mass and height measurements are performed using a digital scale with a stadiometer (Welmy, Santa Bárbara d’Oeste, Sao Paulo, Brazil). The calculation of the body mass index (BMI) is performed using the equation: BMI = body mass (kg)/height^2^ (m). Additionally, waist and hip circumferences will be measured using a measuring tape placed around the navel height and the width of the participants’ hips, respectively, to calculate the waist-hip ratio.

##### Physical activity levels

The self-reported physical activity level will be measured at baseline and post-intervention using the Godin-Shephard Leisure-Time Physical Activity Questionnaire. The Brazilian Portuguese culturally adapted and reliable version of the Godin-Shephard questionnaire will be used [57]. Participants should report the number of times they engage in vigorous, moderate, and light physical activities for more than 15 min per week. The weekly frequencies of intense, moderate, and light activities should be multiplied by nine, five, and three, respectively. The total weekly leisure activity is calculated in arbitrary units from the sum of the products of each component, allowing for to categorization of the individual as insufficiently active or active.

##### Eating habits

The Food Frequency Questionnaire (FFQ) will be used to monitor eating habits. According to the Brazilian Food Guidelines, foods are divided into two groups: in natura/minimally processed foods and processed or ultra-processed foods. Scores are assigned to these groups based on the frequency with which participants report eating them. The instrument includes a list of 16 foods, and scores are assigned to each based on how often participants report consuming them. The scores can range from 0 to 32 points, with higher scores indicating healthier eating habits. An overall healthy eating score is also calculated by summing the points for all evaluated foods, ranging from 0 to 64 points, where higher scores indicate better eating habits. The instrument is applied at baseline and post-intervention.

##### Monitoring the intensity of training sessions

The session rating perceived exertion (sRPE) will be recorded at the end of the last session of each mesocycle using Borg's Category-Ratio 10 scale [58]. The scale in Brazilian Portuguese ranges from 0 to 10, based on perceived effort levels, with 0 indicating no effort (rest) and 10 indicating maximum effort. The sRPE will be collected 5 min after the end of the session, as Christen et al. [59] reported no significant differences between values obtained 5 and 30 min post-exercise.

##### Satisfaction questionnaire

Each participant will answer 7 questions regarding their perception of the intervention using a 5-point Likert scale, in which “1” means “no total agreement” and “5” means “total agreement”. The questionnaire is administered after the intervention to assess participants' perceptions of study satisfaction and safety, as well as benefits for daily life and lifestyle changes.

##### Adherence assessments

Attendance will be monitored through the session’s frequency recording and expressed as the percentage of intervention sessions experienced by a participant, given the total number of scheduled sessions.

#### Plans to promote participant retention and complete follow-up

To improve participant retention and ensure complete follow-up, consistent and clear communication will be maintained with participants to keep their engagement, offer online encouragement, and provide ongoing support to reduce dropouts. Additionally, detailed records of any discontinuation or deviation from intervention protocols, including data collected from participants in these situations, will be kept, ensuring a thorough and transparent analysis of study results.

### Data management

Data are collected on standardized paper forms or through a digital Google Form using a tablet. The method (paper or digital) will be selected according to the characteristics of the questionnaire or test administered, and all data collection will be conducted in person. At the end of every testing day, a researcher will verify missing or inaccurate data and the backup data. Subsequently, double data entry will be conducted for primary, secondary, and additional outcomes.

### Statistical methods

Descriptive data will be presented as means with standard deviations and/or 95% confidence intervals, or as absolute or relative frequencies, when applicable. Generalized Estimating Equations (GEE) will be used to compare primary and secondary outcomes, assuming an unstructured working correlation matrix. In all GEE models, group and time will be treated as categorical variables, and group × time interactions will be included to test intervention effects. Bonferroni-adjusted post hoc tests will be applied when multiple comparisons are performed. The efficacy of the trial will be assessed using a single pre-specified primary outcome and a single primary comparison, consistent with SPIRIT recommendations for clinical trial protocols. Therefore, no multiplicity adjustment across outcomes will be applied. Analyses of secondary outcomes will be considered exploratory, and multiplicity adjustments will be applied only for multiple comparisons within the same outcome (e.g., Bonferroni-adjusted post hoc tests).

Both per-protocol (PP) and intention-to-treat (ITT) analyses will be conducted. In the analysis following the ITT principle, all randomized participants are analyzed in the group to which they were initially assigned, regardless of adherence, treatment receipt, or protocol deviations. Multiple imputations will be used to impute missing data using a specific function on SPSS software. Additionally, PP analyses will be performed to evaluate the robustness of the findings and the effect of adherence to the intervention. Therefore, participants must have at least 70% attendance during the 12-week intervention to be included in the PP analysis. This threshold was defined to ensure sufficient exposure to the training stimulus to plausibly induce adaptations, while accounting for the variability in attendance commonly observed in exercise interventions involving older adults. This cutoff has been adopted in previous aquatic exercise intervention studies conducted by our research group involving older populations under similar conditions [22].

No additional analyses, such as subgroup or sensitivity analyses, are planned for this trial. All statistical procedures will be performed in the SPSS vs. 28.0 program, and the significance level adopted is α = 0.05. Additionally, between-group effect sizes will be calculated using Cohen's d based on change scores and classified as small (≥ 0.2), moderate (≥ 0.5), or large (≥ 0.8) [60, 61].

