### Outcomes

The primary outcome of the study is executive function (verbal fluency subtype), assessed by the Controlled Oral Word Association Test (COWAT; total F-A-S score), which captures aspects of inhibitory control, cognitive flexibility, and verbal initiation. The primary endpoint is the post-intervention time point. The primary analysis will focus on between-group differences at post-intervention, with additional longitudinal analyses examining changes from baseline and the maintenance of effects at follow-up (12 weeks after the end of the intervention).

The secondary outcomes of the study will be presented as group means and include:

Cognitive function, which will be assessed at baseline, post-intervention, and at the 12-week follow-up after the end of the intervention time points:Attention span and short-term memory, measured by the Digit Span Test – Forward (DST–F);Processing speed and visual attention, measured by the Trail Making Test – part A (TMT–A);Executive function (set-shifting ability), measured by the Trail Making Test – part B (TMT–B);Self-perceived cognitive failures, measured by the Cognitive Failures Questionnaire (CFQ).

Physical Function, which will be assessed at baseline and post-intervention time points:Aerobic fitness, measured by the 6-min Walk Test (6MWT);Lower limb strength, measured by performance in the 30-s Chair Stand Test;Upper limb strength, measured by performance in the Arm Curl Test;Lower limb flexibility, measured by the Sit-and-Reach Test (Wells Bench);Agility and dynamic balance, measured by performance in the Timed Up and Go (TUG) Test;Dual-task performance, measured using the TUG combined with a simultaneous cognitive task.

Cardiovascular parameters, which will be assessed at baseline and post-intervention time points:Office blood pressure, measured using a calibrated and automated oscillometric device;Heart rate variability, measured using a heart rate monitor;Blood pressure reactivity, measured using the auscultatory method during the Stroop Test for 3 min;Heart rate reactivity, measured using a heart rate monitor during the Stroop Test for 3 min.

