### Randomization

The randomization sequence will be generated on the website www.random.org, with a 1:1:1 proportion and stratified by age group (60–67 and 68–75 years), and MMSE scores (categorized as with or without cognitive decline) by a researcher not involved with recruitment, data collection, or intervention. The sequence is based on randomly sized blocks that are not disclosed to ensure concealment.

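### The primary GEE names no baseline COWAT covariate and neither stratification factor, so the post-intervention comparison is unbiased but less precise than it need be

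*Protocol article*

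**What the plan says.** - **Model** (Statistical methods): "In all GEE models, group and time will be treated as categorical variables", with their interaction as the test of intervention effects. The GEE is fitted "assuming an unstructured working correlation matrix". No covariate is named. Missing values are to be multiply imputed, and no additional or sensitivity analyses are planned.
- **Primary contrast** (Outcomes): "The primary analysis will focus on between-group differences at post-intervention, with additional longitudinal analyses examining changes from baseline". The outcome is verbal fluency, "assessed by the Controlled Oral Word Association Test (COWAT; total F-A-S score").
- **Randomisation** (Randomization): allocation is 1:1:1 and "stratified by age group (60–67 and 68–75 years), and MMSE scores (categorized as with or without cognitive decline").
- **Effect size** (Statistical methods): Cohen's d is "based on change scores and classified as small", moderate or large at 0.2, 0.5 and 0.8. The divisor is not given.
- **Status of the text** (Open science, Protocol and statistical analysis plan): the article states that it presents the entire protocol together with its analysis plan.

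**The concern.** Baseline COWAT enters the model as a level of time, that is, as an outcome and not as a covariate. Group, time and their interaction form a saturated mean model: each arm has its own free mean at each visit. An unstructured working correlation then has nothing to borrow from baseline when the data are complete or imputed. The post-intervention contrast reduces to the raw difference in post means, and the interaction contrast to the raw difference in mean change. Regressing the post value on baseline gives a smaller variance than either, for any correlation above 0 and below 1.

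The two stratification factors are also absent from the model. Stratification limits how far the arms can differ on those factors, but an unadjusted standard error takes no credit for it.

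Precision is what is at stake. With 28 to 34 women per arm, any avoidable loss matters. A raw post contrast also passes any chance imbalance in baseline COWAT straight into the estimate.

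**Working it through.** **Inputs from the article.** Three arms at 1:1:1; f = 0.180, 90% power, alpha 5%; N = 84, raised to 102 for dropout (Sample size). Per arm: 84/3 = 28 and 102/3 = 34.

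**Inputs assumed.** The baseline–post correlation ρ is not stated; 0.5 to 0.8 is used. The 0.5 SD difference is a benchmark chosen for illustration, not a figure from the article.

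**Step 1: the plan's own figure.** N = 84 reproduces as a repeated-measures ANOVA within–between interaction with 3 groups, 3 time points and ρ = 0.5 (time points and ρ are my assumptions):
- λ = f²·N·m/(1−ρ) = 0.0324 × 84 × 3/0.5 = 16.33, on 4 and 162 df, gives power 0.909.
- N = 81 gives 0.897, so 84 is the first multiple of three above 90%.
- Two time points with ρ = 0.6 also lead to 84.

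On this reconstruction the trial was sized for the interaction.

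**Step 2: what the stated model estimates.** A group × time GEE with unstructured correlation was fitted to two simulated complete data sets. In the first, the post contrast was −0.3389 and the raw difference in post means −0.3389; the interaction contrast was −0.1350 and the raw change-score difference −0.1350. The second data set agreed in the same way (0.2236 and 0.2236; −0.0753 and −0.0753).

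**Step 3: variance.** With equal variances at the two visits, the variance factor per arm is:
- raw post: 1
- change score: 2(1−ρ)
- baseline-adjusted: 1−ρ²

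The ratio of adjusted to change score is (1−ρ²)/[2(1−ρ)] = (1+ρ)/2.

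| ρ (assumed) | Change | Adjusted | Saving vs raw post | Saving vs change |
|---|---|---|---|---|
| 0.5 | 1.00 | 0.75 | 25% | 25% |
| 0.7 | 0.60 | 0.51 | 49% | 15% |
| 0.8 | 0.40 | 0.36 | 64% | 10% |

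As a check, 2,000 simulated trials at ρ = 0.6 gave factors of 1.01, 0.85 and 0.68, against 1, 0.80 and 0.64 in theory.

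**Step 4: power for 0.5 SD, 28 per arm, two-sided 5%, no Bonferroni correction.** Noncentral t on 54 df, noncentrality 0.5 × √(28/2)/√(variance factor) = 1.871/√(variance factor).

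| ρ (assumed) | Raw post | Change (interaction) | Adjusted |
|---|---|---|---|
| 0.5 | 45% | 45% | 56% |
| 0.7 | 45% | 66% | 73% |
| 0.8 | 45% | 83% | 86% |

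**Step 5: strata.** The article gives no association of age group or MMSE category with COWAT, so no figure can be derived.

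**Step 6: Cohen's d.** If the divisor were the SD of change, d would be multiplied by 1/√[2(1−ρ)]: 1.00 at ρ = 0.5, 1.12 at 0.6, 1.29 at 0.7 and 1.58 at 0.8.

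**The case against.** The strongest reply is that the plan does use baseline. Intervention effects are tested through the interaction, which is a change-from-baseline contrast, and N = 84 fits that reading. This stands in part. The Outcomes section nevertheless makes the difference at post-intervention primary and change from baseline additional, so the text supports both readings. Under the interaction reading the gain from adjustment is 3 to 11 percentage points of power.

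Four stronger readings are tempting, and the article does not support them:

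- **That power rises from 45% to as much as 86%.** This holds only if the raw post contrast is the test and ρ is 0.8. Against the interaction at the same ρ, the rise is from 83% to 86%.
- **That omitting the strata takes the test a known distance below 5%.** Any such figure needs the share of COWAT variance that the strata explain. The article does not give it, and the link could be weak: ages run only from 60 to 75, diagnosed dementia is excluded, and the MMSE cutoffs are education-adjusted. In the interaction contrast a stratum effect that is constant over time cancels within each woman. Once baseline COWAT is in the model, the strata have less left to explain.
- **That the reported d will be inflated.** The divisor is not stated. A change-score difference divided by the baseline SD also fits the wording, and with the SD of change there is no inflation at ρ = 0.5.
- **That the result would be biased.** Randomisation keeps both unadjusted contrasts unbiased.

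It can also be said that the text never excludes covariates. True, but it describes itself as the complete plan and foresees no further analyses, so the silence cannot be assumed to be filled elsewhere.

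**Conclusion.** The concern holds as a loss of precision. As written, the primary estimate is either a raw post difference or a change-score difference, and baseline adjustment improves on both. For an assumed correlation of 0.5 to 0.8, the variance saving is 10–25% if the interaction is the test and 25–64% if the raw post contrast is. These figures rest on equal variances at the two visits, complete or imputed data and 28 women per arm. Leaving out the strata errs, if anything, on the conservative side for the post-intervention test, by an unknown amount. The Cohen's d point is a missing definition, not a demonstrated error. The change should be made, but validity does not depend on it.

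**What to change.** Estimate the primary contrast at post-intervention, and the contrast at follow-up, from one of two models:

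- post-intervention and follow-up values as outcomes, with baseline value × time as a covariate; or
- all visits as outcomes, with baseline means constrained to be equal across arms. This keeps the planned changes from baseline available.

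In either model include age stratum and MMSE stratum. Name the contrast from that model as primary and report the adjusted difference with its 95% CI. Use the same form for the secondary outcomes, at the visits where each is measured.

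State the divisor of Cohen's d, preferably the pooled baseline SD, so that the 0.2/0.5/0.8 labels do not depend on the baseline–post correlation.

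The cost is one sentence in the analysis section and a few degrees of freedom. Every variable is already collected, and recruitment is expected to run to August 2027, so the change can be fixed before any unblinded analysis.

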Although the benefits of dual-task aquatic exercise for older adults are promising, it has not yet been proven whether the inclusion of cognitive tasks provides superior gains in cognitive function compared to the same aquatic exercise program alone. On the other hand, the inclusion of cognitive tasks could interfere with gains in physical fitness and associated mechanisms due to limited attentional capacity [41]. Moreover, little is known about how this approach may affect cardiovascular health and psychosocial outcomes, including symptoms of anxiety and depression, sleep quality, and quality of life. Additionally, the latest global consensus on exercise recommendations for older adults emphasizes that multicomponent interventions, which include cognitive tasks, contribute to improving cognition and functional capacity during aging [12]. Thus, interventions involving aquatic exercise programs that provide adaptations in various components of physical fitness, conducted in combination with cognitive tasks, emerge as an innovative strategy, aligned with current recommendations for healthy aging. Therefore, there is a lack of randomized clinical trials with high methodological rigor to clarify these issues, despite the importance of the topic for the health of older adults.

Therefore, we aim to examine the effects of a 12-week aquatic aerobic exercise program combined with cognitive tasks on cognitive function, physical function, cardiovascular, and psychosocial parameters in older women, compared to a conventional aquatic aerobic exercise program and a control group. We hypothesize that both exercise programs will significantly enhance the measured outcomes compared to the control group. Additionally, we expect the aquatic aerobic exercise program with cognitive tasks to have a more pronounced positive effect on cognitive function, as well as on cardiovascular and psychosocial parameters, compared to conventional aquatic aerobic exercise, with similar responses in physical function.

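### The plan rests efficacy on one primary comparison but never names the two arms, and its stated test of intervention effects does not match the post-intervention endpoint

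*Protocol article*

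**What the plan says.** All references are to the protocol article.

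- **Statistical methods, the claim.** "The efficacy of the trial will be assessed using a single pre-specified primary outcome and a single primary comparison". This is the only mention of a primary comparison, and no arms are attached to it.
- **Statistical methods, the test.** In the GEE models, "group × time interactions will be included to test intervention effects".
- **Statistical methods, multiplicity.** "Bonferroni-adjusted post hoc tests will be applied when multiple comparisons are performed". From the single outcome and single comparison the section concludes: "Therefore, no multiplicity adjustment across outcomes will be applied". For the secondary outcomes, "multiplicity adjustments will be applied only for multiple comparisons within the same outcome (e.g., Bonferroni-adjusted post hoc tests").
- **Outcomes.** The primary outcome is the COWAT F-A-S total. "The primary endpoint is the post-intervention time point". The contrast is given only in general terms: "The primary analysis will focus on between-group differences at post-intervention, with additional longitudinal analyses". Maintenance at follow-up belongs to those additional analyses.
- **Background (repeated in the Abstract).** "We hypothesize that both exercise programs will significantly enhance the measured outcomes compared to the control group". The combined programme is also expected to do better than the conventional one on cognitive function.
- **Sample size.** f = 0.180, 90% power and alpha 5% give 84 participants, raised to 102. The test behind the figure is not named.
- **Open science.** The article says that it contains the whole protocol and the statistical analysis plan.

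**The concern.** A three-arm trial has three pairwise contrasts, and the hypotheses use all of them. A claim of one pre-specified comparison has content only if the arms are named. Here the reader has an outcome and a time but no contrast.

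The stated test of intervention effects adds a second difficulty. An interaction over three visits asks whether the arms differ in profile anywhere after baseline. It can be significant because of the follow-up visit alone, which is not the primary endpoint.

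The confirmatory claim is at stake. After the data are in, efficacy could be argued from the interaction, from one unadjusted pair called the single comparison, or from Bonferroni-adjusted pairs. The text does not settle which. The arms chosen also strongly affect power, so the 90% in Sample size cannot be tied to any particular claim.

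**Working it through.** **1. The plan's own figure, N = 84.**

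Inputs from the article: f = 0.180, alpha 0.05, k = 3 groups, m = 3 COWAT visits. Assumed, because the article gives neither: correlation rho = 0.5 and epsilon = 1.

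Repeated-measures group × time interaction:
- df1 = (k − 1)(m − 1) = 2 × 2 = 4
- df2 = (N − k)(m − 1) = 81 × 2 = 162
- λ = N·m·f²/(1 − rho) = 84 × 3 × 0.0324/0.5 = 16.33
- Power from the noncentral F = 0.909

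So 84 reproduces as the 4-df interaction. It is not the only route. Two visits with rho = 0.6 also give 84, as does a 1-df time effect with two visits and rho = 0.5. A one-way comparison of three arms at a single visit with f = 0.180 would need 396. Recruitment: 84 × 1.2 = 100.8, which is 102 in multiples of three.

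**2. Can the interaction signal an effect when the primary endpoint shows none?**

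Assume 28 per arm (84/3), change-score SD 1 and correlation 0.5 between the two change scores. Let there be no effect at post-intervention and an effect e at follow-up in one arm only.
- Sum of squared deviations of the arm means from their average = (2/3)e²
- Follow-up element of the inverse covariance = 1/(1 − 0.25) = 4/3
- λ = 28 × (2/3)e² × (4/3)
- Critical value of chi-square on 4 df = 9.49

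| e (SD) | λ | Rejection rate |
|---|---|---|
| 0.5 | 6.22 | about 49% |
| 0.8 | 15.93 | about 91% |

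These values of e are illustrations. The article uses 0.5 and 0.8 only as labels for moderate and large effects.

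**3. Familywise error on COWAT when no arm differs.**

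Three equal arms, large-sample pairwise z tests, 2,000,000 simulated draws:

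| Rule | Chance of at least one false claim |
|---|---|
| One pair named in advance, 0.05 | 5% |
| Three pairs, Bonferroni (0.05/3 = 0.0167) | 4.4% |
| Two exercise-versus-control pairs, each at 0.05 | 9.0% |
| Best of three pairs, unadjusted 0.05 | 12.2% |

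**4. How much the choice of arms matters.**

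Take f = 0.180 as the 3 × 3 interaction effect, with arm effects present after baseline. The SD of the arm effects is 0.18/√(2/9) = 0.382. With rho = 0.5 the change-score SD is √(2 × 0.5) = 1, so differences in arm effects are already d. Power is from the noncentral t, two-sided, 28 per arm. Both patterns of arm effects are assumed.

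| Pattern | Contrast | d | Power at 0.05 | Power at 0.0167 |
|---|---|---|---|---|
| Arms evenly spaced | Combined vs conventional | 0.47 | 40.5% | 24.5% |
| Arms evenly spaced | Combined vs control | 0.94 | 93.0% | 84.4% |
| Only combined differs | Combined vs conventional | 0.81 | 84.5% | 71.1% |

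At 34 per arm (102/3, no dropout), the two combined-versus-conventional rows become 47.6% and 90.8% at 0.05.

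**The case against.** A reader might infer that the plan abandons multiplicity control. It does not. The waiver is limited to adjustment across outcomes, and Bonferroni is kept for comparisons within an outcome. Three arm comparisons on COWAT fall under that rule, which holds familywise error near 4.4%. The 12% is therefore not the error rate of the plan as written. It needs one pair to be picked after the data are seen and exempted from the rule.

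A reader might also infer that a single comparison and Bonferroni contradict each other. The Bonferroni sentence is conditional on several comparisons being made, so one comparison would not trigger it. What is missing is a statement of whether the primary test lies inside or outside the rule.

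A third tempting reading is that the 4-df interaction is the declared efficacy criterion. No section says so or makes it a gate, and a difference at follow-up alone would not meet the endpoint in Outcomes. Nor does the match with N = 84 prove it, since other settings give the same number.

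All of this narrows the point without removing it. Outcome, visit and within-outcome adjustment are fixed, but the two arms are not. Nor can the gap be left to a separate analysis plan, because the article says the plan is included. Which arms to choose remains the investigators' decision.

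**Conclusion.** The point holds in this limited form. The article claims a single pre-specified comparison that it does not identify, beside three pairwise hypotheses. Its stated test of intervention effects (4 df, follow-up included) does not correspond to the post-intervention endpoint, and the scope of the Bonferroni rule for the primary comparison is unstated.

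Familywise error lies between about 4.4% (the planned Bonferroni over three pairs) and about 12% (one pair selected afterwards and left unadjusted). The interaction could reject in about 49% to 91% of trials with only a follow-up effect of 0.5 to 0.8 SD in one arm. The error rates rest on large-sample normal tests with equal arms. The rejection rates rest on the assumed effects and correlation, and the power figures on the assumed correlation and pattern of arm effects.

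This should be corrected before outcome data are analysed. Recruitment is expected to run to August 2027 and no interim analysis is planned, so there is time.

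**What to change.** In Outcomes and Statistical methods, choose one of two routes.

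1. **One comparison.** Name it as a two-arm difference in COWAT total at post-intervention, estimated as a contrast from the GEE model, tested once at two-sided 0.05 and not gated by the 4-df interaction. Combined versus conventional is the question that Background presents as open, so it is the natural candidate.
2. **Several comparisons.** Declare the post-intervention contrasts that are primary, apply Bonferroni across them, and delete the claim of a single comparison.

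Under either route, make the remaining arm contrasts and all follow-up contrasts secondary under the existing within-outcome Bonferroni rule. State that the interaction test carries no efficacy claim. Restate Sample size for the chosen test, with its correlation and expected difference.

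The text change is a few sentences. The real cost is that the 90% power no longer describes the primary test. For combined versus conventional at 28 per arm, power would be 40.5% with evenly spaced arms or 84.5% if only the combined arm differs. Comparisons not named primary can no longer carry the primary claim.
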